## Introduction

### Background and rationale

Motor neuron disease (MND) is a rapidly progressive, fatal neurodegenerative disease that predominantly affects motor neurons from the motor cortex to the spinal cord and causes progressive wasting and weakening of bulbar, limb, abdominal and thoracic muscles. Prognosis is poor and median survival is 2–3 years following symptom onset: only 4–10% survive more than 10 years [1–3]. There is no cure, and riluzole, the sole disease-modifying UK-licensed drug, prolongs median survival for only 2–3 months at 1 year [4]. Given the nature and impact of MND symptoms on daily life and the poor prognosis, psychological distress is relatively common in people living with MND (plwMND). Prevalence rates of up to 44% for depression and 30% for anxiety have been observed, and MND has been reported to be the most frequent cause of assisted suicide [5–7]. Although shorter survival times, poorer quality of life and increased risks of suicide and mortality have been reported in those experiencing psychological distress [8–12], clear evidence-based guidance on improving the psychological health of plwMND within the UK is lacking.

Formal psychotherapy is not routinely part of standard care within services for plwMND in the UK. While the value of informal psychosocial support is highlighted in NICE MND guidelines, particular psychological therapies or approaches are not specified [13]. PlwMND may be able to access formal psychological therapies such as Cognitive Behavioural Therapy (CBT) through Improving Access to Psychological Therapy services [14]. However, typically these cannot meet their specific psychological, physical and communication needs in a timely fashion due to issues such as the rapid disease course and mobility problems limiting access. Furthermore, therapists within Improving Access to Psychological Therapy services frequently lack knowledge of and familiarity with MND – an important factor that was highlighted in our previous qualitative work that examined plwMND’s preferences for psychological interventions [15].

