Secondary outcome measures will be as follows:Hospital Anxiety and Depression Scale [50]: A 14-item self-report measure of depression and anxiety, which provides separate scores for depression and anxiety, as well as an overall score. For the purpose of analysis and, following validation in plwMND and subsequent published recommendations [51], a subset of data will be analysed which omits one item on the depression scale that assesses psychomotor retardation and one item on the anxiety scale that assesses restlessness as these overlap with physical symptoms of MND;Acceptance and Action Questionnaire-II [52]: A 7-item self-report measure of psychological flexibility (an ACT-specific coping measure);EQ-5D-5L [53]: A 5-item self-report measure of health-related quality of life, used to calculate utility scores for use in economic evaluations. Each of the 5 items is rated on a 5-point scale from no problems to extreme problems. This will be collected from both plwMND and caregivers;Non-physical adverse events and physical self-harm;ALS Functional Rating Scale-Revised [54]: The self-administered version of a 12-item measure of function that has been developed for plwMND will be used as an indicator of disease progression;Existential and Psychological subscales of the McGill Quality of Life Questionnaire-R [45]^,2^: These subscales have been included as secondary outcome measures as quality of life in MND (and hence psychological health) has been found to be more associated with psychological/existential factors than physical function/strength [49];Survival at 9 months;Satisfaction with Therapy and Therapist Scale-Revised [55]: A 12-item self-report measure of satisfaction with therapy and satisfaction with the therapist, rated on a 5-point scale from 1 (strongly disagree) to 5 (strongly agree). Six items relate to satisfaction with therapy and six to satisfaction with the therapist;Client Service Receipt Inventory (CSRI) [42] modified for plwMND. This information will be extracted from participants' self-reports, GP medical records and/or MND care centre records, with participants' consent;Quality-adjusted life years and resource use to inform the cost-effectiveness analysis;Zarit Burden Interview [56]: A well-validated 22-item self-report measure of caregiver burden, which will only be collected from caregivers.

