### Sample size

One hundred eighty-eight plwMND will be recruited from approximately 14 sites. This will allow detection of an effect size of 0.44 standard deviations, with a two-sided alpha of 5% and 90% power. This assumes 20% attrition at 6 months post-randomisation [59], an intra-class correlation coefficient of 0.01 among therapists (as used in other psychotherapy trials [60]) in the intervention arm, assuming 1 therapist per site and a correlation of 0.58 between 0 and 6 months post-randomisation for the McGill Quality of Life questionnaire in plwMND [59]. Our sample size is based on a clinically-meaningful pooled effect size of 0.44 standard deviations reported in a meta-analysis of ACT for mental and physical health conditions vs. controls [61], which falls within the range found for quality of life in studies of ACT in long-term conditions [62]. There are no published data with respect to what a clinically important difference is on the McGill Quality of Life Questionnaire-R in plwMND. However, our effect size is consistent with the minimal clinically important difference of 0.5 standard deviations that has been consistently reported for quality of life across different clinical populations [63].

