Additional exploratory analysis will also be undertaken to assess the consistency of treatment effect across the following subgroups: i) severity of depression and/or anxiety at baseline, according to MND-specific clinical cut-offs on the Hospital Anxiety and Depression Scale [51]; ii) patient preference for treatment; iii) use of pharmacological therapy for mood disorder; and iv) disease severity as measured using the ALS Functional Rating Scale-Revised. We will also undertake exploratory analyses in those who score below clinical cut-offs for anxiety or depression at baseline on the Hospital Anxiety and Depression Scale to see whether ACT is beneficial in preventing progression to clinical levels of these symptoms at follow-up. In addition, we will conduct subgroup analyses to examine the potential impact of the COVID-19 pandemic on the reliability of trial results (with cut points for before and after the beginning of national lockdown on 23 March 2020 and before and after the final easing of lockdown restrictions on 27 January 2022).

The impact of non-adherence (i.e. non-uptake of ACT in the intervention group) and contamination (i.e. delivery of psychological therapy in the control group) will be assessed using complier-average causal effect analysis and a per-protocol analysis. Average Causal Response analysis will be used to assess any incremental impacts of the number of ACT sessions received [65].

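### Exploratory check of effect consistency by baseline depression and anxiety is set on HADS cut-offs; testing the interaction on the collected scores would usually keep more information

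*Protocol article*

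**What the plan says.** The Quantitative analysis section introduces the subgroup work thus: "Additional exploratory analysis will also be undertaken to assess the consistency of treatment effect across the following subgroups". The first of four items is "severity of depression and/or anxiety at baseline, according to MND-specific clinical cut-offs on the Hospital Anxiety and Depression Scale". The following sentence plans "exploratory analyses in those who score below clinical cut-offs for anxiety or depression at baseline", to see whether ACT prevents progression to clinical levels. That sentence suggests one cut per scale but does not settle it.

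Under Outcomes, the HADS is described as a measure "which provides separate scores for depression and anxiety, as well as an overall score". For analysis, one item is dropped from each subscale because it overlaps with MND symptoms. Numeric baseline scores are therefore available for both depression and anxiety. The article mentions no analysis of effect modification on those scores.

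**The concern.** A cut-off treats two people just either side of the line as different, and everyone on the same side as alike. If the benefit of ACT changes gradually with baseline distress, that discards information on the very question being asked.

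The eligibility criteria set no minimum level of distress, so participants can fall on both sides of the cut-offs. Whether the effect varies with baseline mood bears on who might be offered the therapy. The stated aim is to assess consistency, and for that aim low power does harm: an interaction that is missed tends to be reported as a consistent effect. Any avoidable loss of power pushes towards that reading.

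**Working it through.** **1. The plan's own figure.** Inputs from Sample size: "an effect size of 0.44 standard deviations, with a two-sided alpha of 5% and 90% power", 20% attrition, a therapist intra-class correlation of 0.01 with one therapist per site at about 14 sites, and a baseline to 6-month correlation of 0.58.
- Per arm, unadjusted: 2 × ((1.960 + 1.282)/0.44)² = 108.5.
- Baseline adjustment: 108.5 × (1 − 0.58²) = 108.5 × 0.6636 = 72.0.
- Clustering, with about 5.1 to 5.4 analysed per therapist: 72.0 × 1.041 to 1.044 = 75.0 to 75.2.
- Attrition: divided by 0.80 = 93.8 to 94.0, so 94 per arm and 188 in total.

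The stated 188 reproduces. After attrition, 188 × 0.80 = about 150 are analysed.

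**2. Share above the cut-off.** The article gives no expected share for this trial. As a proxy I use Background and rationale: "Prevalence rates of up to 44% for depression and 30% for anxiety have been observed". These are upper figures from the literature and are not stated to use the MND-specific cut-offs.

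**3. Information kept by one cut.** For an interaction that is linear in the score, the relative efficiency of a binary split is the squared correlation between the indicator and the score. For a normal score with a share p above the cut, this is φ(z)²/(p(1 − p)), where z is the cut point in standard units.

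| p above cut | information kept | loss | 150 is worth |
|---|---|---|---|
| 0.50 | 0.637 | 36% | 95 |
| 0.44 | 0.631 | 37% | 95 |
| 0.30 | 0.576 | 42% | 86 |
| 0.20 | 0.490 | 51% | 73 |

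Under the normal model a median split is the best case. If fewer participants than the proxy suggests are above the cut, the loss grows.

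**4. Power.** Take an interaction with 80% power on the score, so the expected test statistic is 1.960 + 0.842 = 2.80. On the split it becomes 2.80 × √0.576 = 2.13 at p = 0.30, or 2.80 × √0.631 = 2.23 at p = 0.44. Power is then about 57% and 60%.

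**5. Smallest difference between subgroups detectable with 80% power** (150 analysed, r = 0.58, clustering ignored).
- Split: SE = √(4 × 0.6636/(150 p(1 − p))) = 0.290 at p = 0.30 and 0.268 at p = 0.44. Multiplied by 2.80, this is 0.81 and 0.75 SD.
- Score: SE per SD of score = √(4 × 0.6636/150) = 0.133, and 2.80 × 0.133 = 0.372. The gap between group means, φ(z)/(p(1 − p)), is 1.66 and 1.60 SD of score. On the same contrast this gives 0.62 and 0.60 SD.

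**6. How far the loss depends on the assumptions.**
- Skewed scores (rounded gamma, mean 5, assumed range 0 to 18) with 17% to 49% above the cut: about 32% to 41%.
- A case defined as above the cut on either scale, with correlation 0.4 to 0.7 between scales, compared with the sum score: 41% to 46%.
- Three ordered severity bands: about 19% to 38%, depending on band sizes.
- A true step in effect at the cut-off: no loss from splitting. The same squared correlation then works against the linear test.

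**The case against.** The strongest case for the plan is that the cut-offs are prespecified, published and specific to MND. They were not chosen from the data, they are easy for clinicians and commissioners to read, and they match the companion analysis of progression to clinical levels, which needs a threshold. The article gives no model or test for the subgroup comparison and refers to a later statistical analysis plan, so a score-based test is not ruled out. All of this stands as a reason to keep the cut-offs in the report. It does not remove the point, because the cut-off form is written into the protocol text itself.

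Three stronger readings are tempting and are not supported.
- A reader might quote a flat loss of 40%. The figure needs one cut per scale, a near-normal score, a linear change in effect and the literature prevalences, none of which the article establishes for this trial.
- A reader might extend the criticism to "disease severity as measured using the ALS Functional Rating Scale-Revised". That item is listed among the subgroups, but no cut is fixed, so there is nothing stated to correct.
- A reader might treat baseline distress as the trial's main moderator question. The article lists it as one of four subgroups and labels the analysis exploratory.

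It is also fair to say that a false reading of consistency is largely a matter of sample size. Even on the score, the detectable difference of 0.60 to 0.62 SD exceeds the 0.44 SD the whole trial is designed to detect.

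**Conclusion.** The point holds as a minor, low-cost improvement. The stated method groups participants by HADS cut-offs although the scores are collected. With one cut per scale, an approximately normal score, a roughly linear change in effect and 30% to 44% above the cut, grouping loses about 37% to 42% of the information on the interaction. The smallest detectable difference rises from 0.60–0.62 SD to 0.75–0.81 SD. The loss is smaller with three bands and nil with a true step.

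Neither version has adequate power for modest interactions, so a non-significant result from either is not evidence of a consistent effect. The primary analysis, the sample size of 188 and the separate analysis of progression to clinical levels are not affected.

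**What to change.** State that effect modification by baseline mood will be tested by adding the continuous baseline HADS score and its interaction with treatment to the primary mixed model. Do this separately for the depression and the anxiety score, with a quadratic or spline term as a check for non-linearity. Report the estimated treatment effects, with confidence intervals, below and above the MND-specific cut-offs for interpretation. Add that a non-significant interaction will not be described as a consistent effect.

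The cost is a sentence or two of analysis wording, with no new data. The downside is the linearity assumption, which the non-linearity check and the retained cut-off display address.

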### Eligibility criteria for plwMND

Inclusion criteria:1. Aged 18 years and over.2. A diagnosis of definite, laboratory-supported probable, clinically probable, or possible familial or sporadic ALS (which is diagnostically synonymous with MND [38] using the World Federation of Neurology’s El Escorial criteria [39], and additionally the progressive muscular atrophy and primary lateral sclerosis variants where appropriate investigation has excluded mimics of MND.

Exclusion criteria:1. A current clinical need for any form of gastrostomy feeding or non-invasive ventilation (NIV). A clinical need is defined as the participant being dependent upon percutaneous endoscopic gastronomy (PEG) to meet all their nutrition and hydration needs or meeting NICE criteria for the offer of a trial of NIV, as defined in Sect. 1.14.17 of NICE Clinical Guideline NG42 [13]. Potential participants who use PEG feeds or receive NIV at earlier points in the disease course because of local practice or for reasons other than their MND diagnosis will not be excluded.2. A diagnosis of dementia using standard diagnostic guidelines [40, 41].3. Currently receiving ongoing formal psychological therapy delivered by a formally trained psychologist or psychotherapist, and unwilling to refrain from engaging in such formal psychological therapy during the receipt of ACT.4. Insufficient understanding of English to enable engagement in ACT and completion of screening measures and patient-reported outcome measures.5. Lacking capacity to provide fully informed written consent, verbal consent (for those who cannot provide written consent), or consent via the use of a communication aid.6. A need for treatment for severe psychiatric disorder such as schizophrenia or bipolar disorder, or expressing suicidal ideation with active plans/suicidal behaviours and imminent intent (hereafter defined as reports of plans to end one's life within the next 2 weeks).7. Other medical factors that could compromise full study participation such as intellectual disabilities or severe sensory deficits (e.g. visual blindness).8. Previous participation in Phase 1 of the COMMEND study (an uncontrolled feasibility study).

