## Usual multidisciplinary care

UC will comprise standard care as outlined in NICE Clinical Guideline NG42 for MND [13], as this is currently what is available within UK healthcare services for plwMND. This will include medication for managing MND and MND-related symptoms, treatments for MND-related symptoms (e.g. physiotherapy, non-invasive ventilation and gastrostomy), and equipment and adaptations to aid activities of daily living, communication and mobility. Coordinated care will be delivered by multidisciplinary healthcare professionals within MND and palliative care services and will include access to other services (including clinical psychology and neuropsychology, counselling, social care, respiratory ventilation, palliative care gastroenterology, orthotics, mobility/assistive technology/communication equipment services and community neurological care teams). All of the MND Care Centres/clinics involved as recruiting sites are endorsed by the MND Association, and therefore are audited against the standard of care outlined in NICE Clinical Guideline NG42 [13].

As some variations in UC may occur, this will be monitored using a modified form of the Client Service Receipt Inventory (CSRI) [42]. Participants in the intervention arm will be asked to refrain from engaging in concurrent formal psychological therapies such as CBT during the receipt of ACT as this may lead to conflicts in therapeutic approaches and goals. Other than this, participants will not be actively discouraged from seeking treatment outside of the trial for ethical reasons, but all such interventions will be recorded as part of the modified CSRI.

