## Measures of bias

The following measures of bias will be included:Credibility/Expectancy Questionnaire [57]: A 6-item self-report measure that assesses the credibility of the rationale for therapy and expectations about treatment, which has been adapted for plwMND. PlwMND will be asked to rate four items on a 9-point scale from 1 to 9 (lower scores are worse) and 2 items are scored on an 11-point scale from 0 to 100%;ACT Treatment Integrity Coding Manual [43]: A coding system that has been developed to assess treatment integrity in ACT interventions, which has been used in previous RCTs of ACT [58]. In this coding system, the frequency and depth of coverage of major components of ACT, together with overall adherence and overall therapist competence, are rated on a five-point scale from 1 (not at all) to 5 (extensively);Treatment preferences: Prior to randomisation, plwMND will be asked to rate how much they would hope to receive ACT plus UC and how much they would hope to receive UC alone. They will be asked to rate this on a 4-point scale from 0 (not at all) to 3 (completely);Assessment of blindness at 6 and 9 months: Although plwMND will be asked not to reveal their allocation to blind outcome assessors, some plwMND may accidentally reveal this and some outcome assessors may be able to guess this. Consequently, outcome assessors will be asked at 6 and 9 months to guess whether they think the participant was allocated to the intervention or control arm and to indicate how certain they are of this using a 5-point scale from 0 (not sure at all) to 4 (very sure);Contamination in the control arm: Use of pharmacological or psychological therapies in the control arm will be monitored using the CSRI. Additional exploratory data analysis will be undertaken to assess the impact of this, if necessary.

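### Control-arm psychological therapy is labelled contamination for the CACE and per-protocol analyses, although the protocol allows it within usual care

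*Protocol article*

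**What the plan says.** All references are to the protocol article.

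- **Quantitative analysis.** Control-group psychological therapy of any kind is contamination: "contamination (i.e. delivery of psychological therapy in the control group) will be assessed using complier-average causal effect analysis and a per-protocol analysis". The next sentence plans an Average Causal Response analysis whose dose is the number of ACT sessions. The primary analysis is by intention to treat.
- **Usual multidisciplinary care.** Coordinated care "will include access to other services (including clinical psychology and neuropsychology, counselling, social care" and further services. Only one arm is restricted: "Participants in the intervention arm will be asked to refrain from engaging in concurrent formal psychological therapies such as CBT during the receipt of ACT". Apart from that, "participants will not be actively discouraged from seeking treatment outside of the trial for ethical reasons", and what they use is recorded on the modified Client Service Receipt Inventory (CSRI).
- **Eligibility criteria for plwMND, exclusion 3.** Being in formal therapy excludes a person only if that person is currently receiving it "and unwilling to refrain from engaging in such formal psychological therapy during the receipt of ACT". Someone in therapy who is willing to pause it can enrol, be allocated to UC and carry on.
- **Measures of bias.** The contamination entry is wider: "Use of pharmacological or psychological therapies in the control arm will be monitored using the CSRI", with exploratory analysis if needed.

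**The concern.** The same therapy is permitted care in the comparator under one section and a deviation under another. The stated objective compares ACT plus UC with UC alone, so therapy reached through UC belongs to the comparator.

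The label has consequences because it is tied to two methods. For a CACE to take account of contamination as defined, controls who had psychological therapy must be coded as treated. That is sound only if their therapy acts on the outcome as ACT does. The protocol argues the contrary: the Background presents ACT as distinct from CBT in approach and techniques, and the UC section asks the ACT arm to pause other therapy because approaches and goals may conflict. A person who would have counselling under UC but ACT under the intervention then receives two different treatments coded as one, and the exclusion restriction fails for that person. Asking only the ACT arm to pause other therapy also strains monotonicity: someone who stops therapy on allocation to ACT and then takes up little ACT would be treated under UC and untreated under ACT.

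A per-protocol set that dropped these controls would select on a post-randomisation event in one arm only.

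At stake is how large an effect of ACT among those who take it up is reported beside the primary result.

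**Working it through.** **1. The plan's own figure.** The 188 in the Sample size section reproduces. With baseline correlation 0.58 the residual variance is 1 − 0.58² = 0.6636. For 0.44 SD, two-sided 5% and 90% power, n per arm = 2 × (1.960 + 1.282)² × 0.6636 / 0.44² = 72.03. Analysed participants per therapist are 94 × 0.8 / 14 = 5.37, so the design effect is 1 + 4.37 × 0.01 = 1.0437, giving 75.18 per arm. Allowing for 20% attrition, 2 × 75.18 / 0.8 = 187.95, or 188. Nothing below alters it.

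**2. CACE: inputs.** p is the share of the ACT arm taking up ACT; q is the share of controls counted as treated. Neither is given. The nearest figure for p is the pilot criterion of at least 70% completing two or more sessions. I assume p from 0.7 to 0.9 and q from 0.05 to 0.30. Following the article's definition, other therapy is counted as receipt in the control arm only.

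**3. CACE: formulas.**
- Receipt means ACT only, no ACT in controls: CACE = ITT / p.
- Control-arm therapy also counts: CACE = ITT / (p − q).
- Ratio of the second to the first: p / (p − q).

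| p | q | p/(p − q) |
|---|---|---|
| 0.90 | 0.05 | 0.90/0.85 = 1.06 |
| 0.85 | 0.10 | 0.85/0.75 = 1.13 |
| 0.85 | 0.20 | 0.85/0.65 = 1.31 |
| 0.85 | 0.30 | 0.85/0.55 = 1.55 |
| 0.70 | 0.30 | 0.70/0.40 = 1.75 |

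For scale, an ITT difference of 0.44 SD at p = 0.85 and q = 0.20 becomes 0.44/0.65 = 0.68 SD instead of 0.44/0.85 = 0.52 SD.

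**4. Dependence on the target.** Now let the effect of ACT against no therapy be 0.44 SD, and let control-arm therapy have a fraction k of it. Then ITT = 0.44 × (p − kq). At p = 0.8 and q = 0.2:

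| k | ITT | ITT/p | ITT/(p − q) | Last column against 0.44 |
|---|---|---|---|---|
| 0 | 0.352 | 0.440 | 0.587 | +33% |
| 0.5 | 0.308 | 0.385 | 0.513 | +17% |
| 1 | 0.264 | 0.330 | 0.440 | 0% |

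Against ACT plus UC versus UC, the target of ITT/p, the inflation is 33% in every row. Against ACT versus no therapy it disappears when k = 1.

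**5. Per-protocol.** Let s be how far the excluded controls fall below the retained controls, in SD. Dropping them raises the control mean by q × s and lowers the treatment difference by as much. With q from 0.05 to 0.30 and s from 0.2 to 0.8 (assumed), the shift runs from 0.05 × 0.2 = 0.01 to 0.30 × 0.8 = 0.24 SD, or 2% to 55% of 0.44. If the excluded controls do better than the rest, the sign reverses.

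**The case against.** The strongest reply is that nothing primary is touched. The intention-to-treat analysis keeps all UC therapy in the comparator and answers the stated objective. CACE and per-protocol analyses are supplementary, and asking what ACT does against no therapy is a legitimate supplementary question. Therapy can be permitted for ethical reasons and still be examined in a sensitivity analysis. This stands, and it limits the weight of the point. It does not remove the need to say which contrast the CACE estimates.

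Second, UC offers access to psychology services, not a course of therapy, and the Background says formal psychotherapy is not a routine part of care for this population. The control-arm rate may be low; at q = 0.05 and p = 0.9 the factor is only 1.06. This stands too.

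Third, a reader might infer that controls who had therapy will be removed. The article does not say so: it says the impact will be assessed, a CACE drops nobody, and the per-protocol set is not defined here. The coding of receipt and that set may be in the analysis plan, which is not shown. Their absence is no finding. What the article does fix is the definition of contamination and the methods attached to it, and a plan that follows it inherits the conflict.

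Fourth, the two contamination descriptions differ in scope more than they clash. Drug use has its own sensitivity and subgroup analyses, so this is mainly loose use of one label.

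**Conclusion.** The inconsistency holds: the contamination definition in Quantitative analysis conflicts with the description of UC and with exclusion 3. Its effect on results is conditional. If non-ACT therapy in controls is coded as treatment received, the CACE for ACT plus UC versus UC is inflated by p/(p − q), 1.06 to 1.75 over the assumed ranges. If a per-protocol set excludes these controls, the difference could move by about 0.01 to 0.24 SD in either direction.

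A reader might go further and conclude that both analyses are biased, and in opposite directions. The documents do not support that. CACE bias is nil for ACT versus no therapy if control-arm therapy works as well as ACT, and the per-protocol direction depends on whether the controls concerned do worse or better than the rest, which the documents do not tell us. The conflict in the text is certain; the size of any bias is not, since p, q, k and s are all assumptions. The primary analysis and the sample size of 188 stand.

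**What to change.** In Quantitative analysis, and in the analysis plan to match:

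- Define treatment receipt for the CACE as receipt of ACT in either arm, in line with the Average Causal Response analysis, which already counts ACT sessions.
- Keep other psychological therapy in the UC arm as part of the comparator. Do not make it a per-protocol deviation; report its use by arm from the CSRI.
- If an ACT-versus-no-therapy analysis is wanted, name it as a separate supplementary estimand and state its assumption that control-arm therapy has the same effect as ACT.
- Reconcile the contamination wording across Usual multidisciplinary care, Measures of bias and Quantitative analysis, including whether drug treatment falls under it.

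The cost is wording. The notes to Table 1 show that a CSRI question on psychological therapy is asked at 6 and 9 months. Whether it separates ACT from other therapies is not shown; if it does not, ACT obtained outside the trial could not be identified. The price in results is a CACE estimate that may be less favourable to ACT.
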